**Objective:**

The aims of this multi-method study are to explore patients’ experiences with injury (and their care) using a focus group study. Then, in the observational study, different courses of ASD, PTSD, and quality of life will be examined. In addition, this study will examine if these courses could be characterized by socio-demographic, clinical, and psychological variables. Consequently, a risk profile will be developed to determine which patients are at risk for developing ASD or PTSD during the 12 months after injury.

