In addition to QOL, PTSD, anxiety, and depression are most frequently examined after injury [15-20]. However, information about ASD is scarce. The existing studies of ASD and PTSD are often cross-sectional. Moreover, in the case of an observational prospective design, examination of PTSD is limited to only several months after trauma. One or several measurements are needed to examine patients’ psychological recovery shortly after injury. Important information about the courses of ASD and PTSD (ie, main scores of onset and development, such as the stability of symptom severity over time) and patients’ characteristics is lacking [8,24,25]. More specifically, it is unknown if and in what way patients’ experiences with injury and treatment, for instance, in the shock room, contribute to psychological consequences. Moreover, factors related to communication between medical staff and patient, treatment of injury, and environment are not known. Gaining information about the development of ASD and PTSD and their sustaining risk factors will increase the quality of care because patients at risk can be offered psychological treatment, thereby preventing the development of psychological disorders, such as ASD and PTSD. Health care providers with the knowledge of medical and psychological consequences after trauma can better anticipate patients’ needs so that patient-centered care can be provided.

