This multi-method study consists of a focus group study and an observational prospective study. The ultimate goal of this multi-method study is to provide valuable insight into the severity of psychological consequences, including ASD and PTSD, and the need for a psychological intervention study to prevent PTSD. First, focus groups are held to examine patients’ experiences with injury (and their care). In this way, potential factors related to the development of psychological problems (eg, depressive symptoms) and disorders (eg, anxiety, ASD, and PTSD) can be obtained and taken into account for the observational study (aim 1). Subsequently, an aim of the observational study is to examine the courses of ASD and PTSD (aim 2). In addition, it will be examined which socio-demographic (ie, sex, age, marital status, and education level), clinical (ie, type of trauma, Injury Severity Score (ISS), Glasgow Coma Score, being hospitalized, being treated on the intensive care unit, complications during treatment, and treatment by a medical psychologist or psychiatrist), and psychological variables (eg, anxiety, depressive symptoms, and personality) characterize the courses of ASD and PTSD. Subsequently, a risk profile will be developed to determine which patients are at risk for ASD and/or PTSD (aim 3). Finally, to study the effect(s) of the natural course of ASD symptoms on the development of PTSD, anxiety and depressive symptoms, and QOL across time will be analyzed (aim 4).

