##### Additional Assessments

Socio-demographic information (ie, sex, age, marital status, and education level) will be obtained from patients at baseline. Clinical information, including date of trauma treatment, ISS, type of trauma mechanism (eg, traffic accident or fall), type of injury (eg, fracture), trauma treatment (eg, operation or medication), consult or treatment from medical psychology (yes/no and which type of treatment), hospital stay (yes/no), in case of hospital stay, admission to intensive care unit, and duration of hospital stay will be abstracted from the patients’ medical records. Possible logistic problems will also be recorded.

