#### Observational Study

The patient characteristic will be studied using descriptive statistics. Then, the baseline characteristics (ie, sociodemographic, clinical, and psychological variables) of participants versus nonparticipants, participants who complete versus drop out during follow-up, and participants who are discharged versus being in the hospital after treatment in the shock room will be compared using independent t-tests and Chi-squared tests. Nonnormal continuous data will be analyzed with Mann-Whitney U tests or Fisher’s exact tests.

Repeated measures of latent class analysis will be used to analyze the courses (ie, time is independent variable) of ASD and PTSD (dependent variables). Moreover, to examine if these different courses of ASD and PTSD (independent variable) could be characterized by socio-demographic (eg, sex, age, education level, and living situation) and clinical (eg, type of trauma, ISS, Glasgow Coma Score, being hospitalized, being treated on the intensive care unit, complications during treatment, and treated by a medical psychologist or psychiatrist), and psychological (eg, anxiety, depressive symptoms, and personality) variables (dependent variables). As a result, each class will represent a different course of ASD and PTSD. By focusing on the characteristics of the different classes, a risk profile will, consequently, be developed to determine which patients are at risk for ASD or PTSD. Sociodemographic and clinical variables are examined as moderating effect, while psychological variables are studied as mediating effects.

Linear mixed models, repeated measures, will be used to examine the effect of ASD (independent variable) on PTSD, anxiety and depressive symptoms, and QOL domains (dependent variables) over time (see Table 2).

The ISS, type of injury and type of trauma mechanism (eg, traffic accident or fall) will be used as covariates. 

**Table 2 table2:** Overview of statistical analysis

Baseline analysis and aims^a^	Independent variables	Dependent variables	Analyses
Patient characteristics	Sociodemographics	N/A^b^	Frequencies Descriptives
	Clinical variables	N/A	Frequencies Descriptives
	Psychological variables	N/A	Frequencies Descriptives
Comparison of patient characteristics	Participants versus nonparticipant	Sociodemographics Clinical variables Psychological variables	Continuous data: Independent t-test, Mann-Whitney U Categorical data: Chi-squared, Fishers’ exact test

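### Psychological or psychiatric care feeds the risk profile for ASD and PTSD, although it plausibly results from the symptoms being predicted and has no time window

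*Protocol article*

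**What the plan says.** The Introduction of the Protocol article, in setting out aim 3, lists among the clinical variables "complications during treatment, and treatment by a medical psychologist or psychiatrist". The Statistical Analysis section for the observational study repeats the list with "complications during treatment, and treated by a medical psychologist or psychiatrist", and then states the use, which covers PTSD as well: "By focusing on the characteristics of the different classes, a risk profile will, consequently, be developed to determine which patients are at risk for ASD".

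The profile looks forward. The Abstract's objective is to determine "which patients are at risk for developing ASD or PTSD during the 12 months after injury", and the Discussion says the profile may serve to predict who is at risk. The Introduction gives the practical purpose: quality of care will rise "because patients at risk can be offered psychological treatment".

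Under Additional Assessments the item is taken from medical records as "consult or treatment from medical psychology (yes/no and which type of treatment"). No date or period is attached to it. In the same section the socio-demographic data "will be obtained from patients at baseline"; the clinical data carry no such wording.

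**The concern.** A risk profile should rest on what is known about a patient before the outcome develops. Psychological care is different in kind from sex, age or ISS, because patients are likely to receive it when they already show the symptoms that define the outcome. It may also change the later course. A profile that contains it partly describes who was recognised and referred, not who was at risk.

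The intended use makes this circular. If the profile helps decide who is offered psychological treatment, having received that treatment cannot be one of its entries. At the point of use the item is either not yet known or already answers the question.

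**Working it through.** The plan gives no figure on this point to reproduce. The check sets the passages side by side and then asks whether the direction of the distortion can be known.

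**1. Does the item enter the profile?** Yes. It stands in the list of clinical variables in both the Introduction and the Statistical Analysis section, and the latter derives the profile from the characteristics of the classes. This is stated in the text and is not a detail left open.

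**2. Is the item confined to baseline?** Nothing confines it. Additional Assessments ties only the socio-demographic data to baseline. The same list of clinical items includes the length of hospital stay, which is not known at the baseline questionnaire for a patient still admitted; participation is confirmed 1 to 5 days after the first consent (Study Procedures). The courses run from inclusion to 12 months. As described, an early consult and a therapy months later would both be coded yes.

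**3. Does such care follow symptoms?** This is plausible, but the documents do not show it for the cohort. The one described route is under Data Collection, Focus Groups: severe symptoms seen in a session led to the physician being informed, who could refer to Medical Psychology. It supports the mechanism at one of the two hospitals, in the other part of the project.

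**4. Can the sign of the association be known?** A simulation of 400,000 patients, with all values assumed:
- early and late symptoms standardised, correlation 0.6;
- log-odds of receiving care = -2.2 + s × early symptoms;
- care lowers late symptoms by b standard deviations;
- high-symptom class = late symptoms above 0.6745, which is 25% of patients when b = 0, the lower end of the 25-33% in the Abstract;
- odds ratio = (treated and high × untreated and not high) / (treated and not high × untreated and high).

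| Referral strength s | b = 0 | b = 0.3 | b = 0.6 |
|---|---|---|---|
| 0.5 | 1.65 | 0.97 | 0.58 |
| 1.0 | 2.45 | 1.47 | 0.88 |
| 1.5 | 3.24 | 1.94 | 1.14 |

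Care never worsens symptoms in any cell, yet the apparent odds ratio runs from 0.58 to 3.24. These figures show only that the sign is open. They do not estimate what this study will find, because the documents give neither referral rates nor a treatment effect.

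**5. Do the neighbouring items share the problem?** Hospitalisation, intensive care and complications follow from the injury and its treatment. No passage makes them a result of ASD or PTSD. For them the only question is whether the status or event is known by the baseline assessment.

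**The case against.** Four arguments deserve weight.

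*Clinical variables are called baseline.* The Statistical Analysis section does refer to "the baseline characteristics (ie, sociodemographic, clinical, and psychological variables"). That sentence concerns the comparisons of participants with nonparticipants, completers with drop-outs, and discharged with admitted patients. It does not govern aim 3. Even a consult before the baseline questionnaire may respond to the acute symptoms that form the start of the course, so the label would not settle the matter.

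*The exact abstraction window belongs in a fuller document.* This is fair as far as it goes, and a missing window alone would not be a finding. The point rests on what the article fixes: this item is a named input to a predictive profile.

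*The analysis is descriptive.* Table 2 makes the courses the independent variable and the characteristics the dependent variables, and the study calls itself exploratory. This stands for the class description, where reporting care received is sensible. It does not stand for the next step, which turns the same characteristics into a statement of who is at risk.

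*A reader might infer that the item will emerge as a strong false risk factor.* The documents do not support that. If 30% of the symptomatic class and 10% of the others received care, the odds ratio would be (0.30/0.70)/(0.10/0.90) = 3.9 with no causal contribution; with 20% and 15% it would be (0.20/0.80)/(0.15/0.85) = 1.4. Both pairs are assumed and leave out any treatment benefit, which pulls the other way. Nor is inflated discrimination shown, since no discrimination measure is planned.

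A reader might also extend the point to aim 4, because treated patients do not show an untreated course. In an observational study, natural course can simply mean that the study imposes no intervention. Adjusting the aim 4 models for treatment over time would not be a safe remedy, since treatment may lie on the path from ASD to later PTSD.

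**Conclusion.** The point holds for one variable. Psychological or psychiatric care is named as an input to a profile of future risk, although it plausibly responds to the predicted symptoms, is undated, and is the care the profile is meant to help allocate. Its association with the courses cannot be read as a prior risk factor.

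The size and sign of the distortion are unknown from the documents. The conclusion assumes that in the cohort, as in the focus groups, referral depends at least partly on symptoms, and that the clinical items are abstracted as described, without a cut-off at baseline. Hospital status, intensive care and complications raise a timing question only, not reverse causation. The change should be made before the risk profile is developed; it leaves the latent class analysis of the courses untouched.

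**What to change.** - Remove psychological or psychiatric care from the risk-profile predictors in the Introduction (aim 3) and in the Statistical Analysis section. This applies whatever its date, because early care can also be a response to acute symptoms.
- State that risk-profile predictors are limited to information available by the baseline assessment. For complications, admission and intensive care, use the status or events dated up to then.
- Record the date of psychological or psychiatric care when the medical records are abstracted.
- Report that care descriptively for each class, as care received.

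The cost is one date field in an abstraction that is already planned, and a change of wording in two places. The profile may separate the classes less well without this item.

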**Methods:**

Trauma patients treated in the shock room (in 2015) of the Elisabeth-TweeSteden Hospital will share their experiences with injury in the focus group study. Open, axial, and selective coding will be used to analyze the data. Concerning the observational study, patients treated in the shock room (during 2016 and 2017, Elisabeth-TweeSteden Hospital and Erasmus Medical Centre) will be asked to participate. The inclusion period is 12 months. Participants will complete the Impact of Event Scale-Revised, MINI-plus, the Hospital Anxiety and Depression Scale, and the World Health Organization Quality of Life-BREF after inclusion and at 3, 6, 9, and 12 months after injury. The NEO-Five Factor Inventory and the State-Trait Anxiety Inventory-Trait are completed after inclusion only. Repeated measures of latent class analysis and linear mixed models will be used to examine the research aims.

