## Introduction

Due to registration and implementation of specialized trauma care, the quality of medical treatment has been improved and survivorship has been increased [1-6]. Trauma is related to physical disabilities (eg, pain, fatigue and impaired wound healing), acute stress disorder (ASD), posttraumatic stress disorder (PTSD), and psychological distress [7-13]. Moreover, trauma patients experience an impaired quality of life (QOL) compared to the general population [14-20].

About 25% of trauma patients have subsyndromal ASD during hospitalization and about 30% had PTSD one month after injury [8,21]. Six months after injury, 49% showed a delayed onset of PTSD. This percentage decreased to 20% at 24 months after injury. A recent systematic review showed that patients diagnosed with ASD had a higher risk of developing PTSD [8]. However, the prevalence rate of patients with ASD who develop PTSD is unknown. Diagnostic criteria for ASD and PTSD are similar; however, dissociative symptoms (eg, depersonalization, derealization, and dissociative amnesia) are only emphasized in ASD and not in PTSD. Moreover, ASD can only be diagnosed within the first month after trauma and last for less than a month, while PTSD symptoms persist for at least one month after injury [22]. PTSD symptoms may begin either after trauma or months or years afterwards [23].

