#### Observational Study

The emergency doctor or the resident will ask patients to participate in this study as soon as they can talk and are lucid. If the emergency doctor or the resident is not able to ask the patient to participate (eg, due to transferring the patient to another department in the hospital), the researcher will ask the patient as soon as possible to participate in this study. The researcher will check medical records to see whether there are patients that have not yet been asked to participate in the study.

Patients will sign two informed consents. First, in the emergency department (after being treated in the shock room and being informed by the doctor). Then 1-5 days later, the patient will be asked to confirm participation again to make sure that they have sufficient time to consider participation in the study. In the case of a patient who is unconscious, the patient will be informed by the researcher and asked to participate as soon as the patient is lucid. If a patient declines participation by not signing the second informed consent, all obtained information will be destroyed.

After confirming participation, the patient will complete a questionnaire on socio-demographic questions, ASD and PTSD, anxiety and depressive symptoms, personality, and QOL at the first time-point (ie, baseline). Clinical information will be retrieved from patients’ medical records. The measurement points are at inclusion, 3, 6, 9, and 12 months after injury (see Figure 1). 

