#### Observational Study

Data for the observational study will be collected using a structured interview—MINI-plus for ASD and PTSD—as well as self-report questionnaires: (1) the IES-R for ASD and PTSD, (2) HADS, (3) NEO Five-Factor Inventory (NEO-FFI) and the State Trait Anxiety Inventory (STAI) - Trait scale for personality, and (4) World Health Organization Quality of Life assessment instrument-Bref (WHOQOL-Bref) for QOL. All outcome measures will be assessed after treatment in the shock room (baseline), 3, 6, 9, and 12 months after injury. However, ASD and personality will only be measured at baseline (see Table 1).

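### For ASD, the psychological part of the aim 3 risk profile is cross-sectional, so it cannot support a claim about who is at risk of developing ASD

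*Protocol article*

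**What the plan says.** Aim 3 in the Introduction asks which socio-demographic, clinical and "psychological variables (eg, anxiety, depressive symptoms, and personality) characterize the courses of ASD and PTSD". The Statistical Analysis section for the observational study repeats the list and turns it into a profile: "By focusing on the characteristics of the different classes, a risk profile will, consequently, be developed to determine which patients are at risk for ASD", followed by PTSD. The same paragraph gives the psychological variables a mediating role and the sociodemographic and clinical variables a moderating one. The Objective in the Abstract describes the profile as identifying patients who will develop either disorder in the year after injury, and the Discussion speaks of prediction.

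On timing, the Data Collection section says "ASD and personality will only be measured at baseline". The Introduction gives the reason for ASD: "ASD can only be diagnosed within the first month after trauma". Under Study Procedures, "the patient will complete a questionnaire on socio-demographic questions, ASD and PTSD, anxiety and depressive symptoms, personality, and QOL at the first time-point". The Methods paragraph of the Abstract agrees for personality: "The NEO-Five Factor Inventory and the State-Trait Anxiety Inventory-Trait are completed after inclusion only". HADS is repeated at 3, 6, 9 and 12 months.

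**The concern.** A statement that a characteristic puts a patient at risk of developing a disorder needs the characteristic to be known before the disorder is observed. The plan applies one list of characteristics and one wording to ASD and PTSD, but the schedule provides that time order for only one of them. PTSD is followed to 12 months, so baseline scores come first. ASD is observed once, at the visit where the psychological scores are taken.

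If the plan is followed as written, a high baseline anxiety or depression score found together with ASD could be reported as a risk factor for ASD, or as a mediator on the way to it. It could equally be part of the same acute reaction or a result of it. Aim 4 itself treats anxiety and depressive symptoms as things that ASD affects. One simultaneous measurement cannot separate these readings. What is at stake is what the study may conclude about ASD, the disorder on which it says knowledge is scarce.

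**Working it through.** No figure in the plan bears on this point, so the check sets the measurement times side by side.

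**1. When ASD is observed.** Data Collection: baseline only. Introduction: diagnosable only in the first month, so visits at 3 months and later cannot supply a new ASD outcome. Table 1 lists the MINI-Plus and the IES-R for both disorders at all five time-points, which taken alone would suggest repeated ASD assessment. The two text statements settle it as one assessment.

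**2. When the psychological characteristics are observed.** The analysis section names "psychological (eg, anxiety, depressive symptoms, and personality) variables (dependent variables". Study Procedures and Table 1 give these times relative to ASD:

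| Measure | Scores | Before ASD | Same time-point | After ASD |
|---|---|---|---|---|
| HADS | 2 (anxiety, depression) | 0 | 1 | 4 (3, 6, 9, 12 months) |
| NEO-FFI | 5 domains | 0 | 1 | 0 |
| STAI-Trait | 1 | 0 | 1 | 0 |

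That is 2 + 5 + 1 = 8 named scores, none recorded before ASD.

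**3. What follows for ASD.** The association between ASD and each of these scores is cross-sectional. A mediator has to come between a cause and its outcome. With mediator and outcome recorded together, the data cannot establish that order.

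**4. Which characteristics do precede ASD.** Sex, age, education, type of trauma, ISS and Glasgow Coma Score are fixed before the injury or by it. They are in the same list and can be prognostic for ASD. Intensive care treatment, complications, and treatment by a psychologist or psychiatrist may fall before or after the baseline assessment; the article does not date them.

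**5. What follows for PTSD.** Baseline HADS, NEO-FFI, STAI-Trait and ASD all precede PTSD at 3, 6, 9 and 12 months. The time-order problem does not arise there, provided that baseline and not follow-up HADS is used.

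**The case against.** The strongest reply is that the plan does not propose a separate ASD prediction model. Classes are formed from the joint course of ASD and PTSD to 12 months, and patients' characteristics then describe those classes. Table 2 lists these characteristics as dependent variables for aim 3, which fits description better than prediction. The study also calls itself exploratory. Part of this stands: baseline scores precede most of each course, and description alone would be unobjectionable. But the ASD component of any course is still the baseline assessment, and the article does not stop at description. It promises to say who is at risk for ASD.

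Second, NEO-FFI and STAI-Trait measure dispositions, which exist before the injury even though they are recorded after it. This stands in part. Trait scores are not simply symptom overlap with ASD, but completing them shortly after injury may colour them. The overlap argument is strongest for HADS.

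Third, baseline HADS as a characteristic in aim 3 and later HADS as an outcome in aim 4 can coexist. This stands. The double role is not a contradiction in itself, and the article does not say that follow-up HADS will serve as a risk characteristic.

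A reader might go further in two ways, and the article supports neither. One is to infer that the whole profile says nothing about who will develop ASD; the demographic and injury variables in it precede ASD. The other is to infer that selection for the later intervention study would be misdirected. The Introduction ties that study to preventing PTSD, for which baseline scores do come first.

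**Conclusion.** The plan is wrong as written for one part of aim 3. For ASD, the psychological component is cross-sectional and supports neither the stated claim about risk of developing ASD nor a mediating role. All eight named psychological scores are affected as regards ASD, with the milder reservation for the six personality scores (5 + 1). The demographic and injury variables that precede ASD are not affected, nor is the use of baseline scores for PTSD from 3 months on.

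The conclusion rests on reading ASD as assessed at baseline only, as the text says despite Table 1, and on treating baseline as one time-point. The article does not fix the order of interview and questionnaires within it or say that they fall on the same day. No numerical size can be given for the overlap: the article reports no correlation between these scales and ASD, and the planned latent class analysis would not produce a share of explained variance in ASD.

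**What to change.** Separate the two disorders in aim 3 and in its row of Table 2.

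- **ASD:** report baseline HADS anxiety and depression as concurrent correlates, not as risk factors or mediators. Report NEO-FFI and STAI-Trait with the caveat that they were recorded after injury and may be coloured by the acute state. Limit predictive statements to variables that precede ASD, such as sex, age, education, type of trauma, ISS and Glasgow Coma Score. Clinical variables such as complications or intensive care treatment belong there only if their dates show that they came first.
- **PTSD from 3 months on:** use baseline, not follow-up, psychological scores, together with baseline ASD, as predictors.
- **Wording:** bring the Objective in the Abstract, the analysis section and the Discussion into line with this split.

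This is rewording and needs no new data. The cost is a shorter and probably weaker-looking ASD profile.

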**Figure 1 figure1:**
[figure not shown]
Flowchart of the study design. ASD: acute stress disorder; IC: informed consent; PTSD: Posttraumatic stress disorder; QOL: quality of life.

Concerning the observational study, all adult patients who have been in the shock room at the Emergency Departments of the Elisabeth-TweeSteden Hospital (Tilburg) or the Erasmus Medical Centre (Rotterdam, The Netherlands) are asked to participate. The inclusion period is about 12 months after the start in November 2016.

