### Data Collection

#### Focus Groups

The topic of the interviews are focused on patients’ experiences with the traumatic event (see Study Procedures). In addition, participants were asked to complete socio-demographic questions, the IES-R and the HADS. All focus groups have the same structure and are audio-recorded. The recorded focus groups are transcribed verbatim [26,27].

In case of observed severe symptoms of ASD or PTSD during focus group sessions, the treating physician was informed. The doctor could refer the patient for a consult with a psychologist in the department of Medical Psychology at the Elisabeth-TweeSteden Hospital who is specialized in psychological treatment after injury.

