## Discussion

This is the first multi-method study in trauma patients that examines psychological consequences after injury, using both a qualitative focus group study design as well as an observational prospective design. In the focus group study, the aim was to interview patients about their experiences with the injury, treatment, and rehabilitation. Since it is unknown if and in what way patients’ experiences contribute to the development of psychological problems and disorders. The observational study will examine the course of ASD and PTSD, as ASD after injury is less studied and it is unknown how ASD and PTSD develop over time up to 12 months after injury. Moreover, as a result of all outcome measures, a risk profile of patients may be determined to predict which patients are at risk for developing ASD or PTSD. Altogether, this study will provide information concerning which patients to include in further research that focuses on psychological intervention.

Several factors related to the design and execution must be taken into account. First, response bias may occur in the focus group study. Patients may decline participation because they are not interested in discussing their experiences, or it might be too confronting to talk about their experiences and psychological problems. Second, it is known that the population of trauma patients has a broad variety of trauma mechanisms and injuries. Therefore, it might be difficult to generalize to the whole trauma population. However, concerning the observational study, almost all trauma patients being treated in the shock room will be included from two different Level-1 trauma centers so data saturation can be reached. These centers are located in different provinces and cities in The Netherlands. Therefore, a representative population in the observational study can be included. Third, patients with severe injuries might be less capable to complete the baseline questionnaire almost directly after injury due to being treated at the intensive care unit. Patients will, therefore, be asked to fill in the date of completing the questionnaire and if they needed any help. Then, the time between injury and measurement can be analyzed. This provides information on what time severely injured patients are capable to complete the baseline questionnaire.

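### Patients from two hospitals are pooled, but centre is missing from the stated covariates, so the aim-4 ASD effect is not protected against confounding by centre (minor)

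*Protocol article*

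**What the plan says.** Under Participants and Centers of Recruitment, the Protocol article names the two recruiting sites for adult shock-room patients: "Emergency Departments of the Elisabeth-TweeSteden Hospital (Tilburg) or the Erasmus Medical Centre (Rotterdam, The Netherlands) are asked to participate". The Discussion describes both as Level-1 trauma centres, adds "These centers are located in different provinces and cities in The Netherlands", and takes this as support for a representative sample.

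For aim 4, the Statistical Analysis section (Observational Study) says: "Linear mixed models, repeated measures, will be used to examine the effect of ASD (independent variable) on PTSD, anxiety and depressive symptoms", and also on quality-of-life domains, over time. The adjustment sentence follows directly: "The ISS, type of injury and type of trauma mechanism (eg, traffic accident or fall) will be used as covariates". The example in brackets qualifies only the mechanism, so the list of three covariates is closed as written. The sentence does not say which models it governs. From its position it applies at least to the aim-4 models.

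Centre is also absent from the other places where it could have appeared:

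- **Introduction:** the clinical variables form an exhaustive list, ending in "complications during treatment, and treatment by a medical psychologist or psychiatrist), and psychological variables".
- **Statistical Analysis:** the corresponding list is given by example, with "complications during treatment, and treated by a medical psychologist or psychiatrist), and psychological" variables next, and does not name centre.
- **Group comparisons:** three are planned (participants against nonparticipants, completers against those who drop out, discharged against hospitalised). None is between hospitals.
- **Table 2:** no row includes centre.

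**The concern.** Aim 4 asks what ASD does to later PTSD, anxiety, depressive symptoms and quality of life. Nobody is randomised to ASD, so the answer depends on the adjustment set. Hospital is a design factor of this study, known for every patient, and could be related to both sides of the comparison:

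- **Exposure:** the text of Data Collection says ASD is measured only at baseline. Baseline depends on when staff approach the patient and on a second consent 1 to 5 days later. Local logistics could therefore shift the measured ASD rate.
- **Outcome:** residual case mix or local practice could shift later scores.

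If both happen, a pooled model without centre attributes some of the hospital difference to ASD. The article chose to state its adjustment set, so this is a stated list without centre, not a detail on which the article is silent.

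**Working it through.** **Figures available.** The article gives no ASD rate, outcome or patient count by hospital, so there is no figure of the plan to reproduce on this point. The only effect scale is the effect size of 0.4 under Sample Size Calculation.

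**Formula.** In a linear model that omits a two-level centre variable,

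bias in the ASD effect = g × [P(centre B | ASD) − P(centre B | no ASD)],

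where g is the outcome difference between centres, in SD units, at the same ASD status. The bracket is the imbalance in hospital between patients with and without ASD. Because ISS, injury type and mechanism are in the model, both factors should be read as what remains after those covariates.

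**Inputs, all assumed:**

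- patients split 50:50 or 70:30 between centres A and B;
- ASD 25% at A against 33% at B, or 20% against 35%. The first pair borrows the 25-33% of the Abstract, which covers ASD or PTSD and is not a rate by centre;
- g from 0.1 to 0.5 SD.

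**Imbalance:**

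- 50:50, 25% and 33%: 0.33/0.58 − 0.67/1.42 = 0.569 − 0.472 = 0.097
- 50:50, 20% and 35%: 0.35/0.55 − 0.65/1.45 = 0.636 − 0.448 = 0.188
- 70:30, 25% and 33%: 0.099/0.274 − 0.201/0.726 = 0.361 − 0.277 = 0.084
- 70:30, 20% and 35%: 0.105/0.245 − 0.195/0.755 = 0.429 − 0.258 = 0.170
- equal ASD rates, either split: 0

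**Bias in SD units:**

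| Split | ASD A / B | g = 0.1 | g = 0.3 | g = 0.5 |
|---|---|---|---|---|
| 50:50 | 25% / 33% | 0.010 | 0.029 | 0.049 |
| 50:50 | 20% / 35% | 0.019 | 0.056 | 0.094 |
| 70:30 | 25% / 33% | 0.008 | 0.025 | 0.042 |
| 70:30 | 20% / 35% | 0.017 | 0.051 | 0.085 |
| either | equal | 0 | 0 | 0 |

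The non-zero range is about 0.01 to 0.09 SD. Against 0.4 that is 0.008/0.4 = 2% to 0.094/0.4 = 24%. The percentage is only a rough yardstick, because the article does not say to which contrast or scale the 0.4 belongs.

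**The case against.** The strongest reply is that nothing in the article shows that the hospitals differ in any way that matters. Both are Level-1 centres, and their locations are mentioned to support representativeness. The stated covariates already cover much of the case mix. Patients record the date on which they complete the baseline questionnaire, so timing can be examined. The study calls itself exploratory, and a condensed article often leaves a site term to the analysis plan.

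Most of this stands, and it limits the weight of the point. It does not remove it: the covariate list is stated, centre is not on it, and recording baseline dates or psychological treatment puts neither into the aim-4 model.

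Three stronger readings are tempting, and the article does not support them.

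1. **Psychological care differs between the hospitals.** A reader might infer this from the mention of a "psychologist in the department of Medical Psychology at the Elisabeth-TweeSteden Hospital who is specialized in psychological treatment after injury". That sentence stands in the focus-group section. The focus groups recruited and met only at that hospital, so its referral route is the only one the section would describe. Silence about the other hospital is not evidence about its care.
2. **The risk profile is distorted too.** Treatment by a psychologist could stand in for the hospital where it is easier to obtain, but that presupposes the undocumented difference in care. Aim 3 describes which patients are at risk and estimates no adjusted effect. The variable list in the analysis section is also open, so centre is not excluded there.
3. **The bias reaches a third of the planned effect.** ASD of 15% against 35%, equal centres and g = 0.5 give (0.700 − 0.433) × 0.5 = 0.13 SD, or 33% of 0.4. These inputs are extreme: the centre difference exceeds the effect size used for planning, and the calculation gives the existing covariates no credit.

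**Conclusion.** The point holds as a minor one, confined to aim 4. Two hospitals are pooled, the adjustment set is stated without centre, and no planned analysis compares the hospitals. Confounding by centre needs two things together: ASD frequency and later outcomes must both differ between hospitals after adjustment for ISS, injury type and mechanism. The article neither shows nor excludes this. The size is therefore unknown: zero with equal ASD rates, and about 0.01 to 0.09 SD under the assumed splits, rates and centre differences. The case for change rests on the low cost of a safeguard for a non-randomised comparison, not on a demonstrated bias. Differing psychological care and leakage into the risk profile are plausible but undocumented, and should not be asserted.

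**What to change.** 1. Enter centre as a fixed covariate in each aim-4 linear mixed model. Two levels are too few for a random effect.
2. State which models the covariate sentence governs.
3. Report by centre, descriptively, ASD frequency, time from injury to baseline, the proportion receiving psychological treatment, and class membership. This also gives the Discussion's statement on representativeness a check that it now lacks.

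The cost is one degree of freedom per model in a study planned for 300 patients, plus one descriptive table. No new data are needed: each patient's hospital is known, psychological treatment is already taken from the records, and patients already give the date of the baseline questionnaire.
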